### Plans for collection, laboratory evaluation, and storage of biological specimens for genetic or molecular analysis in this trial/future use {33}

Not applicable. The optional microbiological samples collected in the trial form part of routine care with the result being reported. No samples have been stored for use in the trial or for future use.

## Statistical methods

### Statistical methods for primary and secondary outcomes {20a}

#### Statistical analysis

A separate statistical analysis plan for the quantitative analysis of the C-STICH study will provide a detailed description of the planned statistical analyses. A brief outline is given below. All analyses will be by intention to treat. Every attempt will be made to collect pregnancy outcome data on all women and it is anticipated that missing data will be minimal. Women with missing primary outcome data will not be included in the first instance.

#### Primary analysis

Pregnancy loss will be summarised by treatment arm using frequencies and percentages. A log-binomial model will be used to generate relative risks (and 95% confidence intervals (CI)), adjusting for the minimisation variables. Adjusted risk differences will also be presented (and 95% confidence intervals).

### Interim analyses {21b}

An interim report including the analysis of major endpoints will be provided in strict confidence to a DMEC at intervals of at least 12 months, or to a timetable agreed by the DMEC prior to study commencement. Criteria for stopping or modifying the study based will be ratified by the DMEC. Final analysis will be performed once all women and their babies have reached the end of the follow-up period.

### Methods for additional analyses (e.g. subgroup analyses) {20b}

#### Secondary analysis

Secondary outcomes which are binary will be analysed as per the primary outcome. Continuous outcomes which are deemed to be normally distributed will be summarised using means and standard deviations and a linear model will be fitted to generate adjusted mean differences (and 95% CIs). Continuous outcomes which are not deemed to be normally distributed will be summarised using medians and interquartile ranges and unadjusted differences in medians will be produced with 95% CIs. Time to event data will be summarised using medians and interquartile ranges. A cox regression model will be fitted to generate adjusted hazard ratios (and 95% CIs) and a Kaplan-Meier plot will be produced to assess the data visually. All analyses will be adjusted for the minimisation variables (where possible).

### Methods in analysis to handle protocol non-adherence and any statistical methods to handle missing data {20c}

#### Sub-group analyses and missing data

All sensitivity and subgroup analyses will be limited to the primary outcome only. Subgroup analyses will be limited to indication for cerclage (a history of ≥3 previous midterm losses or premature births (≤28 weeks)/insertion of a cervical suture in a previous pregnancy/a history of mid trimester loss or premature birth with a (current) shortened cervix (≤25mm)/women whom clinicians deem to be at risk of preterm birth either by history or the results of an ultrasound scan), technique planned (with bladder dissection/without bladder dissection), and intention to commence patient on progesterone (yes/no). Sensitivity analyses will consist of an analysis to assess the impact of missing data and an analysis to assess the impact of adherence to the randomisation allocation. This will include an as treated and per-protocol analysis.

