#### Cerclage Placement

The local approved designated C-STICH staff member should report details of the cerclage placement procedure using the Cerclage Placement Form (CRF 2), providing information to include the taking of a microbiological swab, use of and type of antiseptics, technique used, the suture thread used, the number of “bites”, the position of any knots, and use of any tocolytic agent.

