### Assignment of interventions: allocation

#### Sequence generation {16a}

Participants should be randomised just prior to the cervical cerclage procedure, to minimise the number of withdrawals and protocol violations, but allowing sufficient time for the obstetrician to prepare the sutures for the procedure. Birmingham Clinical Trials Unit provide a bespoke web-based randomisation with telephone back-up. Patients are entered and randomised into the trial by logging into secure online webpage available at www.birmingham.ac.uk/C-STICH. Each GCP-trained researcher eligible to randomise will be provided with a unique username and password. The online randomisation is available 24 h a day, 7 days a week apart from short periods of scheduled maintenance and when there are occasional network interruptions. Alternatively, investigators can make a Freephone telephone call (Tel - [name]) to the randomisation service. This telephone randomisation service is available between 0900 and 1700 h Monday to Friday.

A Randomisation Form (CRF1) should be used to collate the necessary information prior to randomisation. All eligibility criteria and baseline data items on CRF1 will need to be answered before a trial number and allocation can be given. If an essential data item is missing, randomisation will be suspended but can be resumed once the information is available. This will be followed by a confirmatory email sent to the randomising person, local Principal Investigator, and the main research staff member within the centre.

Women will be randomised in a 1:1 ratio to either monofilament or braided suture material. A minimisation algorithm will be used to ensure balance in the treatment allocation by site, indication for cerclage (a history of ≥3 previous midterm losses or premature births (≤28 weeks)/insertion of a cervical suture in a previous pregnancy/a history of mid trimester loss or premature birth with a (current) shortened cervix (≤25mm)/women whom clinicians deem to be at risk of preterm birth either by history or the results of an ultrasound scan), technique planned (with bladder dissection/without bladder dissection), and intention to commence patient on progesterone (yes/no). A “random element” will be included in the algorithm, so that each participant has a probability (unspecified here) of being randomised to the opposite treatment that they would have otherwise received.

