### Assignment of interventions: blinding

#### Who will be blinded {17a}

Clinicians cannot be blinded to the allocation. Should suture allocation need to be recorded in the hospital notes to facilitate the placement of the correct randomised suture (e.g. as cerclage is to be performed later by a different clinician), this is acceptable. The suture material used should also be documented within the operation notes. As far as possible, it is preferable that the patient and microbiologists should remain unaware of the treatment allocation. Duration of blinding should continue, where possible, until both mother and baby have reached their respective trial end points (i.e. final follow-up). The primary outcome (miscarriage, stillbirth, termination of pregnancy and neonatal death) is objective and thus should minimise any bias incurred by lack of blinding.

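### The adherence sensitivity analysis names only as-treated and per-protocol analyses, which are biased if suture switching relates to prognosis; add a randomisation-based complier-average estimate

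*Protocol article*

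**What the plan says.** Under Statistical analysis, the protocol article sets the general principle: "All analyses will be by intention to treat". The primary analysis is a log-binomial model adjusted for the minimisation variables.

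Under Sub-group analyses and missing data, it adds a sensitivity analysis described as "an analysis to assess the impact of adherence to the randomisation allocation", and continues: "This will include an as treated and per-protocol analysis". The scope is narrow: "All sensitivity and subgroup analyses will be limited to the primary outcome only". No adherence estimator that uses the randomised groups is named.

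Three other statements bear on this:
- Who will be blinded: "Clinicians cannot be blinded to the allocation".
- Secondary analysis, on adjustment: "All analyses will be adjusted for the minimisation variables (where possible"). Sequence generation lists these variables as site, indication, planned technique and intention to give progesterone. All are known before the operation.
- Cerclage Placement: CRF 2 records the suture actually used.

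**The concern.** Randomisation comes before the procedure, and the article allows that a different clinician may place the suture later. A change from the allocated suture is therefore a decision made after randomisation by someone who knows the allocation, and it could depend on what is found at surgery. If so, the women who switch differ in prognosis from those who do not.

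An as-treated analysis moves such women into the other group. A per-protocol analysis removes them from one group only. Either way the comparison mixes suture with prognosis, and adjustment for pre-surgery variables cannot remove difficulty first met at surgery. The two results could then differ from intention to treat through confounding alone, and a reader could take the difference for the effect of the suture among women who received it.

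**Working it through.** **Inputs from the article.** Allocation is 1:1. The revised total is 2050 women, designed for 90% power and a 41% relative reduction (risk ratio 0.59). The original design used 19% against 11.2%, with 2.5% attrition.

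**Inputs that are assumed.** The switching rate, the prognosis of switchers and the pooled loss rate are not stated.

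**Pooled loss rate.** The standard two-proportion formula (two-sided 0.05, 90% power) with 19% against 11.2% gives 441 per arm, 882 in total, and 882/0.975 = 905, close to the stated 900. The same formula at a risk ratio of 0.59 gives 2000 women, and 2000/0.975 = 2052, when the braided rate is about 9.2% and the monofilament rate 9.2% × 0.59 = 5.4%. The pooled rate is then about (9.2 + 5.4)/2 = 7.3%. This is a back-calculation, not a figure in the article.

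**Bias with no true effect.** Let p = 7.3% be the risk in each randomised arm. Let a share s of the monofilament arm switch to braided, with risk 2p = 14.6%. Take 1000 women per arm.

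- Women who stay on monofilament: (p − s × 2p)/(1 − s)
- Braided as treated: (p + s × 2p)/(1 + s)
- As-treated risk ratio: first divided by second
- Per-protocol risk ratio: first divided by p

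| s | Stay on monofilament | Braided as treated | As-treated RR | Per-protocol RR |
|---|---|---|---|---|
| 2.5% | (7.3 − 0.365)/0.975 = 7.11% | (73 + 3.65)/1025 = 7.48% | 0.95 | 0.97 |
| 5% | (7.3 − 0.73)/0.95 = 6.92% | (73 + 7.3)/1050 = 7.65% | 0.90 | 0.95 |
| 10% | (7.3 − 1.46)/0.90 = 6.49% | (73 + 14.6)/1100 = 7.96% | 0.81 | 0.89 |

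Both ratios are free of p: per-protocol is (1 − 2s)/(1 − s), and as-treated is that times (1 + s)/(1 + 2s). The 7.3% therefore affects precision but not the size of the bias.

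**Direction.** If the same women switch from braided to monofilament instead, the ratios invert. At 5%, as-treated is 1.11 and per-protocol 1.06; at 10% they are 1.23 and 1.13. With equal switching of this kind in both arms, both ratios are 1.00.

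**A harsher pattern.** Suppose 20% of women are hard cases with three times the risk of the rest, switching is from monofilament only, N is 2050 less 2.5%, and the loss rate is 7.3% to 10%.
- If 5% of the arm switches, the per-protocol risk ratio is 0.94 and the as-treated 0.89. A true null is rejected about 7% and 11% to 14% of the time.
- If 10% switches, the ratios are 0.87 and 0.79, with rejection in 12% to 16% and 30% to 40%.
- Intention to treat stays at 5% throughout.

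**A randomisation-based estimate, at 5% switching.** The intention-to-treat risk difference is 0, and the difference in monofilament receipt between arms is 0.95. The complier-average risk difference is 0/0.95 = 0. Complier risk is 6.92% in the monofilament arm and, under the exclusion assumption, (7.3 − 0.05 × 14.6)/0.95 = 6.92% in the braided arm, so the risk ratio is 1.0.

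**The case against.** The strongest reply is that these are conventional sensitivity analyses beside an intention-to-treat primary analysis, and the article gives them no larger role. That stands. A reader might infer that the trial's main conclusion is at risk, or that the plan contradicts its own intention-to-treat statement. The text supports neither, because the adherence analyses are presented as sensitivity analyses of the primary outcome.

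A reader might also infer a bias towards monofilament. The article gives no reason for switching, rate or direction, and the working shows that the sign reverses or vanishes under other patterns. Several provisions also aim at high adherence: randomisation just before the procedure, allocation emails, and the allocated suture kept with the records. At low switching the bias is small. Even at 5% in the first illustration, the as-treated ratio of 0.90 (65.7/950 against 80.3/1050) has an approximate 95% interval of 0.66 to 1.24, a shift of about 0.6 standard errors. Adjustment for indication and planned technique could absorb some of the confounding.

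The article is an outline, its wording does not exclude further methods, and the separate analysis plan, which is not shown, may add one. The absence of a complier-average analysis is therefore not in itself an error. The point is that the methods actually named are the weaker ones.

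Finally, receipt is not strictly all-or-nothing. An additional occlusion stitch is only requested to match the allocation, a second cerclage should ideally match the first, and a woman may receive no cerclage. A complier-average analysis needs a definition of receipt. Under the null it also adds nothing to the intention-to-treat test; its use is to estimate effect size among adherers without breaking randomisation.

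**Conclusion.** The point holds as a low-severity improvement. The two named analyses lose the protection of randomisation and would be biased if switching relates to prognosis, in a direction set by which way harder cases move. Under the stated assumptions the bias is small at 2% to 3% switching and could matter at 5% to 10%. Those sizes rest on assumed switching rates and risks, so they show what could happen and do not predict this trial. The primary analysis and the sample size are unaffected.

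Dropping both analyses, or reporting per-protocol without a confidence interval, would go further than the evidence supports. Removing the interval would hide the very imprecision that guards against over-reading.

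**What to change.** In Sub-group analyses and missing data, add as the main adherence analysis a complier-average causal effect of the suture received at the initial cerclage. Use randomisation as the instrument, report a risk ratio and risk difference with 95% confidence intervals, and adjust for the minimisation variables where possible. Define receipt by the initial cerclage suture on CRF 2, and state a rule for women who receive no cerclage.

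Keep the as-treated and per-protocol analyses with their confidence intervals, labelled as supportive, non-randomised and open to confounding.

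The cost is a short text change and one more model on data already collected. The interval will be wider, and the estimate needs the exclusion and monotonicity assumptions. Adjusting for site in a risk-ratio instrumental-variable model may be difficult across the 75 sites given under Recruitment, hence the wording on adjustment where possible.

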### Plans to give access to the full protocol, participant-level data, and statistical code {31c}

Requests for data generated during this study will be considered by BCTU. Data will typically be available within 6 months after the primary publication.

Only scientifically sound proposals from appropriately qualified Research Groups will be considered for data sharing. The request will be reviewed by the BCTU Data Sharing Committee in discussion with the Chief Investigator and where appropriate (or in absence of the Chief Investigator) any of the following: the Trial Sponsor, the relevant Trial Management Group (TMG), and independent Trial Steering Committee (TSC).

A formal Data Sharing Agreement (DSA) may be required between respective organisations once release of the data is approved and before data can be released. Data will be fully de-identified (anonymised) unless the DSA covers transfer of patient identifiable information. Any data transfer will use a secure and encrypted method.

### Composition of the data monitoring committee, its role, and reporting structure {21a}

#### Data Monitoring and Ethics Committee

##### Determining when clear answers have emerged

If one treatment really is substantially better or worse than any other with respect to the primary outcome, then this may become apparent before the target recruitment has been reached. Alternatively, new evidence might emerge from other sources that any one treatment is definitely more, or less, effective than any other. To protect against this, during the main period of recruitment to the study, interim analyses of the primary outcome and adverse events will be supplied, in strict confidence, to an independent DMEC along with updates on results of other related studies, and any other analyses that the DMEC may request. The DMEC will advise the chair of the TSC if, in their view, any of the randomised comparisons in the trial have provided both (a) “proof beyond reasonable doubt” that for all, or for some, types of patient one particular treatment is definitely indicated or definitely contraindicated in terms of a net difference in the major endpoints and (b) evidence that might reasonably be expected to influence the patient management of many clinicians who are already aware of the other main trial results. The TSC can then decide whether to close or modify any part of the trial. Unless this happens, however, the TMG, TSC, the investigators, and all the central administrative staff (except the statisticians who supply the confidential analyses) will remain unaware of the interim results.

The BCTU Trial office will forward open DMEC meeting minutes to the Sponsor and Funding Body.

Appropriate criteria of proof beyond reasonable doubt cannot be specified precisely, but a difference of at least *p*<0.001 (similar to a Haybittle-Peto stopping boundary) in an interim analysis of a major endpoint may be needed to justify halting, or modifying, the study prematurely. If this criterion were to be adopted, it would have the practical advantage that the exact number of interim analyses would be of little importance, so no fixed schedule is proposed.

The DMEC consists of 3 members independent from the BCTU and sponsor.

[name] (Chair) National Perinatal Epidemiology Unit (NPEU)

[name]—(Consultant Obstetrician) Norfolk & Norwich University Hospital

[name] (Senior Statistician—University of Aberdeen)

### Adverse event reporting and harms {22}

The collection and reporting of adverse events (AEs) will be in accordance with the Health Research Authority’s UK Policy Framework for Health and Social Care. There may be unexpected serious adverse reactions associated with monofilament or braided sutures when used in cervical cerclage. Monofilament or braided sutures have been used to treat cervical cerclage for many years and there is no reason to believe there are adverse biochemical reactions intrinsic to the material of the suture thread, but there may be adverse events arising from the biomechanical properties of the thread. There are also known adverse events of cerclage irrespective of suture material used. It is the responsibility of investigators to notify serious adverse events to the C-STICH Trial Office, who will forward all SAEs to the Chief Investigator. It is the remit of the sponsor or their representative to expedite to the ethics committee within 15 days any serious adverse events (SAEs) that are considered related and unexpected. Where SAEs are expedited to the Research Ethics Committee (REC), the PI will be informed by the C-STICH study team of the RECs response and any actions to be taken.

#### Definitions and reporting requirements adverse events (AE)

An AE is:
Any unintentional, unfavourable clinical sign or symptom such as:Any new illness or infection or the deterioration of existing disease or illnessAny clinically relevant deterioration in any laboratory assessments or clinical tests, for example continued shortening of the cervix or dilatation.

Non-serious AEs do NOT need to be reported to the Trials Office. A SAE is an untoward event which:

Results in maternal death*Immediately threatens the life of participant**Results in hospitalisation or prolongation of existing hospitalisationResults in a persistent or significant disability/incapacityIs an important medical event that may jeopardise the patient or requires medical intervention to prevent one of the outcomes above.

*All maternal deaths will be reported to BCTU on the SAE Form irrespective of whether the death is related to pregnancy, the cerclage procedure, or an unrelated event. If a participant dies, any post-mortem findings must be provided to BCTU. BCTU will report all deaths to the DMEC, CI and sponsor for continuous safety review. All SAEs deemed to be related and unexpected will be expedited to the REC. **Life-threatening in the definition of a SAE refers to an event in which the mother was at risk of death at the time of the event. It does not refer to an event which hypothetically might have caused death if it were more severe. Important AEs that are not immediately life-threatening or do not result in death or hospitalisation, but may jeopardise the pregnancy or may require intervention to prevent one of the other outcomes listed in the definition above, should also be considered serious. All SAEs for the participant and their baby need to be reported to the Trials Office (the only exception being those SAEs listed as exempt from reporting). Assuming they meet the definition of serious, examples of reportable SAEs (which should be reported on the SAE form) are, but not limited to, the following:
Premature rupture of membranes within 48 h of the cerclage procedure.Infection of the amniotic sac (chorioamnionitis) requiring intravenous antibiotics.A miscarriage, preterm delivery, or neonatal death within 48 h of cerclage procedureCervical lacerations at time of cerclage procedureBladder injury as a result of the cerclage procedureRetained suture material at cerclage removalCongenital malformations, abnormalities identified in the neonatal periodPostpartum haemorrhage at or greater than 1500mlAntepartum haemorrhage that requires a cerclage removal.

There are some SAEs associated with the trial that are already well characterised, where it is highly unlikely that the trial will reveal any new safety information relating to the intervention. Recording of these SAEs will not affect the safety of participants or the aims of the trial. As such, the following SAEs are exempt from reporting to the Trials Office:
Admission for routine monitoringRemoval of cervical cerclage more than 48 h after the cerclage procedureTreatment, which was elective or pre-planned, for a pre-existing condition that is unrelated to the pregnancyAdmission to a hospital for delivery of the babyManagement of a premature babyAdmission for observation in cases of threatened preterm labourPostpartum haemorrhage less than 1500mlAntepartum haemorrhage not requiring cerclage removalPremature rupture of membranes after 48 h of cerclage procedurePreterm labour after 48 h of cerclage procedureMiscarriage after 48 h of cerclage procedureCongenital malformations, abnormalities identified on the mid trimester scanPV bleedAnaesthetic complications

A miscarriage, preterm delivery, or neonatal death 48 h after the cerclage procedure will be considered an outcome and not a SAE and should be reported on the pregnancy outcome form. If a site reports an SAE that the Trials Office believes exempt from reporting, clarification will be sought by the Trials Office, with the site asked to review their reasons for reporting. If both parties then agree the SAE is exempt from reporting, the SAE will no longer require processing, though a record of it and the relating correspondence should be kept by both parties. AEs should still be recorded locally in accordance with local practice/SOPs. Reportable SAEs, for both the participant and their baby, from the day of randomisation into the trial, until the defined end of the trial, should be reported to the Trials Office. Whether observed directly or reported by the patient, these must be recorded on CRF 7 within 24 h of the research staff becoming aware of the event. The PI (or nominated investigator (medically qualified doctor) delegated the relevant responsibility on the delegation log) is required to assign causality, signing the SAE form to confirm their assessment. Where an SAE form has been completed by someone other than an investigator, the original SAE form will be required to be countersigned by the Investigator to confirm agreement with the causality. Assessment of causality must be made by an investigator (definition above) according to the definitions in the table below. If an investigator is unavailable, initial reports without causality assessment should be submitted to BCTU by a healthcare professional within 24 h, but must be followed up by medical assessment as soon as possible thereafter, ideally within the following 24 h. If information is missing from the initial SAE report, including ongoing events where there is as yet no end date, the SAE should be followed up until resolution or stabilisation of the event. Follow-up information should ideally be provided on a new SAE Form, using the SAE reference number provided by the BCTU trials team. For all reportable SAEs, the CI or delegate will review the SAE and provide their own assessment of causality. In cases where either the reporting investigator or the CI believes the SAE related the CI or delegate will also perform an expectedness assessment. This expectedness assessment will be based on the clinical judgement/experience of the CI or delegate, with reference where appropriate, to those SAEs listed as expected below. For expectedness assessment purposes, the following will be considered as expected SAEs:
Preterm prelabour rupture of membranes, miscarriage, neonatal death within 48 h of cervical cerclage procedureAntepartum haemorrhage requiring suture removalPostpartum haemorrhage greater than 1500mlRetained suture thread at cerclage removalPostnatal readmission with infection/sepsis

Where there is a discrepancy between the local assessment of causality and the assessment from the CI, neither will be downgraded and both opinions will be documented. If either party believes an SAE related, and the CI believes it unexpected, the SAE will be reported to the REC within 15 days. Details of this will be provided to the relevant site’s PI and should be filed in the relevant section of the Investigator Site File. If an AE is mistakenly reported as an SAE, the site will be informed and the SAE will be downgraded to an AE.

